## Abstract

**Introduction:**

This trial aims to evaluate the impact of the IMPROVA intervention programme in improving mental health, quality of life, and well-being in adolescents enrolled in secondary schools in four European countries.

**Methods and analysis:**

The IMPROVA intervention will be evaluated using a two-arm parallel group pragmatic cluster randomised controlled trial with an intervention and a wait-list control group. Secondary schools in France, Germany, Romania, and Spain were recruited. Originally, we estimated to enrol a total of 6000 students within 64 schools; that is, 16 schools per country. The IMPROVA programme is a multi-level intervention that provides tailored content for adolescents, families, and school staff. This content creates a unified and supportive framework that promotes mental health and social-emotional development among adolescents. A series of implementation strategies was planned to support the uptake of the programme into the education setting and among participants. Study outcomes were assessed at baseline, mid-term (during the intervention), postintervention (primary end point), and will be assessed at postintervention (secondary end-point; 6 months after postintervention). Overall mental health (Strengths and Difficulties Questionnaire) is the primary outcome. Secondary outcomes include: health-related quality of life, depression, anxiety, social isolation, and self-esteem. The trial will be evaluated regarding its effectiveness, cost-effectiveness, implementation, and social return on investment analysis.

**Ethics and dissemination:**

This study has received the approval of human research ethics committees in France (Comité de Protection des Personnes Ile-de-France VIII”, No. 2024-A00201-46), Germany (Ulm University Ethics Committee, No. 186-24), Romania (The Research Ethics Subcommittee of the Babeș-Bolyai University of Cluj-Napoca, No. 14.146/23.09.2024), and Spain (CEIm Fundació Sant Joan de Déu, No. PIC-61-24). Results will be disseminated through peer-reviewed open-access publications and presentations at national and international conferences. Non-technical summaries will be shared with public health authorities, participants, and stakeholder organisations. All findings will be reported in aggregate form, ensuring no individual participant can be identified.

**Trial registration number:**

NCT06556576.

STRENGTHS AND LIMITATIONS OF THIS STUDYA key strength of this study is its rigorous cluster randomised controlled trial design and the theory-driven intervention design grounded in social and emotional learning and cognitive-behavioural frameworks.The IMPROVA programme is developed using a co-creation approach that systematically integrates input from students, school staff and families through qualitative and pilot-testing activities across France, Germany, Romania and Spain.The study has sufficient statistical power to detect changes in primary and secondary outcomes and to support planned effect-modification analyses.Alongside analyses of effectiveness and effect pathways, the study incorporates a comprehensive evaluation of implementation processes, economic impact and social return on investment.A potential major limitation of the IMPROVA programme is the inherent complexity of achieving its systematic integration into school curricula and daily routines across four European countries, a challenge for which multiple implementation strategies have been proactively developed.

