### Sample size

Adolescents are the main unit of analysis of this RCT. Statistical power calculations indicated that 6000 adolescents are necessary to detect small differences (d=0.30) in mental health scores between the control and intervention groups, with 80% power. This calculation considered that schools would have 200 students (cluster size), two measurements, an aggregated intra-class correlation of schools and countries of 0.20, α=0.05, and 50% refusal to participate and loss to follow-up. A total of 6000 adolescents will also allow for stratifying the effectiveness analysis per one characteristic (eg, sex (male, female), socioeconomic status (higher, medium, lower)).

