### School recruitment and selection

Following the estimations for the sample size, we aimed to recruit a total of 64 schools. The IMPROVA team invited secondary education schools in four countries: France (Ile-de-France region); Germany (Baden-Württemberg); Romania (Cluj-Napoca) and Spain (Catalonia). The strategy to select the region of the schools considered the geographical distance from the IMPROVA local team and the inputs of the regional educational administration, while ensuring the socioeconomic representativeness of the region.

The approach to schools was adapted by country, but the procedures generally followed a similar structure, summarised in the following. Schools were contacted via email and/or phone call. After a preliminary conversation (via email or phone) with school directors or a representative, the local IMPROVA team visited the schools to present the project to school directors or the board. Often, the directory board discussed the possibility of collaborating with the project with teachers and sometimes with family and student representatives before signing the collaboration contract.

Significant challenges arose at all trial sites, making it difficult to reach the target number of 64 schools. In total, 51 schools were recruited across the four sites. The breakdown by country is as follows: France: seven schools; Germany: 15 schools; Romania: 15 schools, and Spain: 13 schools. We decided to stop school recruitment since more than 20 000 students attended the 51 participating schools and were potential participants for the IMPROVA RCT. This allowed each trial site to initiate baseline assessments and implementation of the intervention. See an overview of the main challenges per trial site.

*Spain*: A prior agreement between the regional educational department and another mental well-being initiative prevented the authorities from supporting the identification and invitation of schools to participate in the IMPROVA RCT. Consequently, many of the schools in Catalonia were already part of the other mental well-being programme, preventing us from engaging with more schools.

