### Effect modification analysis

We will also evaluate whether the intervention effect varies according to certain characteristics such as participants’ sex, age, country, socioeconomic status, school type, and mental health status at baseline. These analyses will involve testing for statistically significant interaction effects between the intervention and potential moderators within linear mixed models.

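### The unqualified claim of sufficient power for the effect-modification analyses is not supported by the protocol's own inputs for country, which is a between-school moderator

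*Protocol article*

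**What the plan says.** The strengths and limitations list of the protocol article claims "sufficient statistical power to detect changes in primary and secondary outcomes and to support planned effect-modification analyses", without qualification.

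The effect modification section names these moderators: "sex, age, country, socioeconomic status, school type, and mental health status at baseline". Each is to be judged by a significant interaction with the intervention in a linear mixed model.

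The sample size section is the only support for the claim. It says that "6000 adolescents are necessary to detect small differences (d=0.30) in mental health scores between the control and intervention groups, with 80% power", on the basis that "schools would have 200 students (cluster size), two measurements", with "an aggregated intra-class correlation of schools and countries of 0.20, α=0.05, and 50% refusal to participate and loss to follow-up". It adds that "6000 adolescents will also allow for stratifying the effectiveness analysis per one characteristic", and its examples are sex and socioeconomic status, both of which vary between pupils of the same school. It gives no interaction effect size and no interaction power.

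The school recruitment section reports 51 schools against a target of 64, broken down as "France: seven schools; Germany: 15 schools; Romania: 15 schools, and Spain: 13 schools" (these sum to 50). Recruitment was stopped with reference to the number of pupils attending the schools. Randomisation was of schools, blocked within country.

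**The concern.** Every pupil in a school shares the same arm and the same country. The arm-by-country interaction is therefore estimated between schools, and its precision depends mainly on the number of schools per arm within each country. At an ICC of 0.20, more pupils per school add little. The sample size argument is about pupil numbers and pupil-level strata, so it does not carry over to country. School type raises the same issue wherever it is a property of the school.

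The stake is interpretation. The introduction sets out to learn how such programmes can be scaled across populations and educational contexts. A non-significant country interaction, published beside a statement that power was sufficient, invites the reading that the programme works equally in all four countries.

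**Working it through.** **Inputs from the protocol article.** d = 0.30, 80% power, two-sided α = 0.05, ICC 0.20, 200 pupils per school, 50% refusal and loss, 6000 adolescents (sample size section); 7, 15, 15 and 13 schools (school recruitment section).

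**Assumptions.** Arm splits of 3/4, 7/8, 7/8 and 6/7, since schools per arm are not given. A between-country difference in effect of 0.30 SD, since no interaction size is given; it equals the whole target effect. Pupils per school: 59 (3000/51), 100 (200 × 0.5) or 118 (6000/51).

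**1. The plan's own figure.** Without clustering, 2 × (1.96 + 0.84)² / 0.30² gives 175 per arm, or 350.

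| Pupils per school | Design effect 1 + (m − 1) × 0.20 | Analysed | Divided by 0.5 |
|---|---|---|---|
| 200 | 40.8 | 14,280 | 28,560 |
| 100 | 20.8 | 7,280 | 14,560 |
| 46.9 (3000/64) | 10.175 | 3,561 | 7,123 |

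The 6000 is not reproduced. The correlation between the two measurements, which would reduce these totals, is not stated. The calculation is in any case for the main effect only.

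**2. Country contrast, one measurement, ICC 0.20.** The variance of a school mean is v = 0.20 + 0.80/m, which is 0.2068 at m = 118 and 0.2136 at m = 59. The variance of the difference between two countries' effects is v × h, where h sums 1/k over the four country-by-arm groups of k schools.

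- France-Germany: h = 1/3 + 1/4 + 1/7 + 1/8 = 0.851. SE = √(0.2068 × 0.851) = 0.42. Power for 0.30 SD is 11%. The detectable difference is 2.80 × SE = 1.18 SD (1.19 SD at m = 59).
- Germany-Romania: h = 2 × (1/7 + 1/8) = 0.536. SE = 0.33. Power is 14-15%. The detectable difference is 0.93 SD (0.95 SD at m = 59).
- With the planned 16 schools per country, h = 4/8 = 0.5 and the detectable difference is still about 0.9 SD.

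**3. Joint test on 3 df.** The noncentrality is the sum of w × (effect − weighted mean effect)², with w = 1/(v × h) for each country. At m = 118 the weights are 8.3, 18.0, 18.0 and 15.6 (France, Germany, Romania, Spain). If France alone differs by 0.30 SD, the noncentrality is 0.64 and power is 9%. If two countries (France and Germany) differ from the other two by 0.30 SD, it is 1.33 and power is 14%.

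**4. With a repeated-measures gain.** Assume school autocorrelation 0.90 and within-pupil correlation 0.6. For change scores, v = 2 × ICC × 0.10 + 2 × (1 − ICC) × 0.40/m. With adjustment for baseline, v = ICC × (1 − 0.81) + (1 − ICC) × (1 − 0.36)/m. The lower figure is the change score at m = 59, and the upper is baseline adjustment at m = 100.

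| ICC | France-Germany | Germany-Romania |
|---|---|---|
| 0.20 | 30-35% | 44-51% |
| 0.10 | 44-54% | 63-74% |
| 0.05 | 58-74% | 77-91% |

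**5. Lower ICC without that gain** (60 pupils per school, France-Germany): 16% at ICC 0.10, 24% at 0.05 and 40% at 0.02.

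**6. Pupil-level moderator, for contrast.** For a balanced binary factor within schools, SE = √(16 × 0.80/N). With N = 3000 this is 0.065, and 0.18 SD is detectable. With N = 6000 it is 0.046, and 0.13 SD is detectable.

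**The case against.** Four points stand at least in part.

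- **The ICC.** The 0.20 pools schools and countries, while the model fits country as a fixed effect. The relevant within-country ICC may be lower, and at 0.05 with repeated measures some country contrasts approach or pass 80% power. The protocol gives no such figure, so the claim still lacks support, but a range has to be shown.
- **The model as written.** It has a constant school intercept and no school-by-time term, so its group-by-time test nominally removes the school effect. With within-pupil correlation 0.6 and ICC 0.20, v = 2 × 0.80 × 0.40/m. Nominal power is then 88% (France-Germany) and 98% (Germany-Romania) at 59 pupils per school. That gain assumes that schools do not drift differently over time, an assumption nowhere stated, and it leaves the ICC 0.20 basis of the sample size.
- **The benchmark.** The 0.30 SD is an assumed interaction size. It is as large as the whole target effect, and smaller differences have less power.
- **Reporting.** The article already commits to effect estimates with 95% CIs, which is part of the remedy.

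A reader might also infer that testing six moderators at p≤0.05 contradicts a sample size said to serve "will also allow for stratifying the effectiveness analysis per one characteristic", and that a multiplicity correction is missing. Six independent tests would give 1 − 0.95⁶ = 26% chance of at least one false positive. The documents do not support the charge. The phrase reads naturally as one characteristic at a time, which fits separate moderator analyses. The moderator tests are not called confirmatory, and a multiplicity rule for them may stand in an analysis plan that is not shown.

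**Conclusion.** The power statement goes beyond its only basis and, for country, is not supported by the protocol's own inputs. At ICC 0.20 and the recruited schools, power for a 0.30 SD difference is about 11-15% pairwise and 9-14% jointly, or 30-51% pairwise with the assumed repeated-measures gain. The planned 16 schools per country would not have cured this.

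The result rests on the assumed arm splits, interaction size and correlations. It weakens as the within-country ICC falls: 44-74% at 0.10 and 58-91% at 0.05, with the same gain.

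Two stronger readings should be resisted. The claim is not wrong for moderator analyses in general, because pupil-level factors such as sex are well powered. Nor can it be called simply false for country, because the within-country ICC and the size of interaction in view are not stated. For school type the concern applies only where the school fixes it; no figure can be given because the numbers of schools by type are not reported.

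**What to change.** - Limit the power statement in the strengths and limitations list to pupil-level moderators.
- Label country, and school type where it is fixed by school, as exploratory, and report them as interaction estimates with 95% CIs.
- State beside the result the country difference detectable with the recruited schools, with the within-country ICC and correlations used, so that a non-significant interaction is not read as equal effects.
- Reconcile the total of 51 schools with the country list, which sums to 50, since the detectable difference depends on these counts.

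The cost is wording and a short calculation. Design and data collection do not change, but the stated scope of the moderator analyses becomes less favourable.

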## Introduction

 Promoting adolescents’ mental health is pivotal. Notably, approximately half of all mental health problems in adulthood have their onset before or during adolescence.^1^ Furthermore, young people who experience mental health problems before the age of 14 years are more likely to report mental burdens in adulthood.^2^ In addition, mental health problems during adolescence are associated with a higher risk of suicide, which is the second most common cause of death among individuals aged 15–29 years worldwide.^3^ Finally, depression and anxiety are among the top five causes of overall disease burden in this age group.^4^

Schools represent a fundamental setting for implementing interventions to promote mental health and prevent psychological problems in adolescence.^5^ However, most systematic reviews indicate that primary interventions implemented in school settings have weak to modest effects.^6^,^8^ Among the various approaches, universal social and emotional learning (SEL) interventions have the strongest evidence of enhancing young people’s social and emotional skills while also reducing symptoms of depression and anxiety in the short term.^8^

Furthermore, cognitive-behavioural therapy (CBT)-based interventions, both universal and targeted, have demonstrated effectiveness in reducing internalising and externalising symptoms.^69^,^12^ While preventive universal CBT programmes are promising in alleviating symptoms of depression and anxiety in the short term, targeted CBT interventions seem particularly appropriate for young people experiencing mild but detectable depressive symptoms, with effects extending into the medium term (ie, 6 months after the intervention period).^10^ Additionally, while teachers can effectively deliver universal interventions,^13^ there is no strong evidence that teacher-led programmes adequately address the needs of students experiencing symptoms of depression or anxiety.^13^ For these students, CBT-based interventions delivered by external professionals, such as psychologists, provide the most convincing evidence of improving mental health outcomes.^14^ However, the high costs associated with incorporating psychologists into community-based interventions, such as in schools, pose a significant barrier to large-scale implementation.^15^ This challenge underscores the importance of specialised training of teachers or other professionals (eg, primary healthcare, other school staff) in addressing both emerging and more severe mental health difficulties. Considering the state-of-the-art on mental health promotion among youth,^6^,^12^ intervention programmes should integrate SEL’s broad skill-building benefits with CBT’s symptom-focused strategies to create a comprehensive and effective school-based mental health intervention that addresses both universal and targeted prevention.

Despite an expanding body of research supporting school-based mental health interventions, several knowledge gaps remain. Although SEL and CBT-based interventions have been shown to promote mental health and alleviate subclinical symptoms of depression and anxiety among youth, the overall effectiveness of these programmes remains modest, especially in preventive programmes.^6^,^8^ Furthermore, a key limitation is the scant evidence regarding factors necessary to ensure the long-term scalability and effectiveness of such interventions.^8 16^ Importantly, at the population level, the mental health of adolescents continues to deteriorate,^17^ raising concerns about the adequacy of current approaches. Although CBT-based interventions show promise, their scalability is hindered by resource constraints, particularly the high costs of delivering targeted interventions to adolescents with sub-clinical symptoms of mental health problems.^15^ Additionally, universal programmes led by teachers may not adequately address the needs of students with emerging mental health difficulties.^13^

Given the decline in adolescent mental health and the limited effectiveness of current school-based interventions, the American Psychological Association has encouraged a change in focus from an ‘individual-level’ to a ‘population-level’ approach to mental health.^18^ Individual-level policies (i-policies) should be complemented with system-level policies (s-policies) such as community-level interventions, public policies, and system transformation to successfully improve population mental health.^19^ According to Dodge *et al*,^18^ a population-level approach would ensure mental health for diverse population groups and diminish inequalities. To successfully reach this goal, programmes should integrate three key aspects. First, programmes should scale up individual-level interventions that have been proven to be effective using implementation science approaches^18^ and make use of innovative delivery methodologies, such as the internet, mobile applications, machine learning and artificial intelligence, among others.^1820^,^22^ Second, programmes must incorporate novel methodologies and test policy-driven community-level programmes, taking successful examples from public policies promoting physical activity or abolishing corporal punishment in schools.^18^ Third, a new universal primary care model for mental health is needed.^18^

To address the aforementioned limitations of current methods and contribute to substantial advancements in the field, we are conducting the IMPROVA project. IMPROVA stands for ‘e-Intervention Enhancing Mental Health in Adolescents’. IMPROVA represents a leap forward in the field of adolescent mental health and well-being for a number of reasons.

First, the intervention programme is grounded in the principles of SEL interventions and integrates cognitive-behavioural strategies into its content. As such, IMPROVA draws on well-established, evidence-based approaches,^6^,^12^ thereby enhancing its potential effectiveness. Second, rather than addressing only mental problems, the IMPROVA programme focuses on skills and competence training to reduce barriers to access and avoid potential stigmatisation associated with using the platform.^23^ Third, the programme offers a universal intervention with some elements of a targeted intervention that is both accessible and potentially effective for adolescents with subclinical symptoms of depression and anxiety. This combination bridges the gap between universal programmes, which often lack sufficient impact for at-risk youth, and targeted interventions that require external professionals and are resource-intensive.

Fourth, IMPROVA is delivered via a scalable digital platform that enables the consistent delivery of intervention content throughout the year. This is an improvement over relying on a limited number of in-person encounters or workshops. eHealth solutions, such as mobile apps and internet platforms, have the potential to facilitate the implementation of interventions in school settings by allowing for the accessible and continuous delivery of intervention content throughout the school year.^24^ Furthermore, the persuasive design of the IMPROVA platform may increase engagement and intervention adherence, which are two of the main challenges in youth e-mental healthcare.^25^ The platform contains features such as primary task, dialogue, system credibility and social support that aim to increase engagement and adherence through personalised content, UX design, reward and reminder strategies. These features facilitate knowledge and skills acquisition and integrate social learning and social support.^26^ Moreover, compared with interventions delivered in person, eHealth platforms are more scalable and may eventually reduce the costs thanks to their potential for large-scale implementation.^27 28^ In addition, eHealth solutions, especially in school settings, may reduce the gap in access to health and educational resources caused by social inequalities^29^ since internet access is becoming more widespread, especially in the European Union (EU).^30^ Nonetheless, a systematic evaluation of commercially available mobile mental health apps for children and adolescents indicates poor overall app quality and an absence of science-driven development and evidence.^31^

Fifth, the IMPROVA programme offers tailored content for key stakeholders involved in adolescent mental health promotion, including adolescents themselves, school staff, and families. By providing user-specific resources, IMPROVA ensures that each group receives relevant guidance and tools to support mental well-being. In particular, the programme equips school staff with extensive materials to facilitate the implementation of the intervention, balancing professional support with practical application. By delivering tailored material to a diverse range of stakeholders without the need for specialised professionals and resources, IMPROVA was conceived to enhance accessibility and cost-effectiveness while preserving the quality and integrity of the intervention.

Sixth, IMPROVA engaged relevant stakeholders, including adolescents, parents, school staff and policymakers from the very beginning of the project. To enhance the programme’s cultural relevance, we conducted a series of co-creation activities—including meetings, focus groups and pilot testing—with these stakeholder groups in France, Germany, Romania and Spain. Many previous programmes implicitly assumed that vulnerable groups of adolescents (eg, at higher risk of mental health problems, from lower socioeconomic backgrounds or exposed to potentially traumatic events) would benefit most from intervention efforts. However, preliminary evidence suggests that interventions may be ineffective or even harmful in vulnerable groups, thereby increasing their risk of falling (further) behind.^23 32^ IMPROVA’s collaborative process helped tailor the intervention to varied sociocultural contexts, ensuring its acceptability, feasibility, and potential for large-scale implementation.

Taken together, the IMPROVA intervention programme was designed to enable scalable implementation across diverse educational and cultural contexts. It integrates a comprehensive mental health promotion programme within educational settings and extends its reach to adolescents’ families. By leveraging the inherent scalability of eHealth platforms, IMPROVA may reduce the logistical and financial barriers typically associated with large-scale implementation, especially for in-person programmes.^27 28^ A key feature of the programme is its modular structure, which allows for the flexible use of individual components or the full suite of resources. This enables the programme to adapt to various educational and cultural settings, user characteristics and even fluctuations in daily mood. The extensive co-creation methodology applied ensures that the programme is relevant and meaningful to a wide range of population groups, including those from lower socioeconomic backgrounds and those who are culturally underrepresented in mental health research. Through a rigorous, multi-site randomised controlled trial (RCT) and mixed-methods implementation study, IMPROVA will assess intervention effectiveness and generate critical insights into how digital, school-based mental health programmes can be effectively and equitably scaled across different populations and educational contexts.

